### Sample size calculations

2.6

The sample size calculation has been performed using R statistical software (R Core Team). In order to detect relevant differences between groups in the changes from pre-to post-intervention, we determined a sample size sufficient to detect medium effect sizes (Cohen’s *f* = 0.4). Therefore, α = 0.05, and *p* = 0.90, were selected to favor clinically significant effect sizes. The sample size calculation is based on sleep quality as the main variable. A total of 24 participants per group are necessary to examine the hypothesis that interventions impact sleep quality. Two additional participants are included to compensate for possible drop-outs. Each of the four groups will consist of 25 participants, resulting in a total of 100 participants.

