### Statistical analyses

2.7

Data will be analyzed with R statistical software (R Core Team, Austria). The statistical analysis will determine the effects of the three different training interventions on sleep, fitness, cognitive, and quality of life variables compared to a control group. The analysis will include subjects who completed all the pre-and post-tests. If participants drop out or deviate from the intervention protocols, their data will not be used. Deviations will include non-eligibility, withdrawal of consent, missed test visits, and intervention protocol not completed. Data from the pre-test and post-test will be presented using descriptive statistics: mean, standard deviation, and percentage to describe the participants’ characteristics and performance on assessments. Comparisons within and between four groups at baseline and post-intervention will be done using repeated measures ANOVA, after checking for normality. Assessments will be considered as the dependent variables, and the group will serve as the independent variable. *Post hoc* analyses will be conducted when a significant main effect is observed using Tukey’s test to correct for multiple comparisons.

The initial ANOVA, comparing the PET, PET, and BLE, control group, will aim to assess the presence of intervention effects (pre/post). The hypothesis is that the combined PET and light interventions will result in improved outcomes in both groups compared to the control group across various domains, including physical and motor fitness, cognitive, QoL, circadian rhythms, and sleep variables.

The second ANOVA, comparing the GVS and control groups, will be designed to assess the existence of intervention effects (pre/post). The hypothesis is that the GVS intervention will lead to improvements in balance, cognition, QoL, circadian rhythms, and sleep variables compared to the control group.

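### Tukey comparisons depend on a significant main effect, but the effect the trial targets is the group-by-time interaction, which the plan never names

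*Protocol article*

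**What the plan says.** All of this is in the protocol article.

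- **Model** (2.7 Statistical analyses): "Comparisons within and between four groups at baseline and post-intervention will be done using repeated measures ANOVA, after checking for normality".
- **Factor** (same section): "Assessments will be considered as the dependent variables, and the group will serve as the independent variable". Time is not listed as a factor, and no interaction is mentioned.
- **Rule for pairwise comparisons** (same section): post hoc "analyses will be conducted when a significant main effect is observed", with Tukey's test as the correction for multiplicity.
- **Target** (2.6 Sample size calculations): the trial is sized "In order to detect relevant differences between groups in the changes from pre-to post-intervention".

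Section 2.7 then describes two ANOVAs. The first has three groups (PET, PET + BLE, control) and the second has two (GVS, control). Each is meant to assess intervention effects, glossed as pre/post.

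**The concern.** In a two-occasion repeated-measures ANOVA, a difference between groups in change is the group-by-time interaction. Neither main effect measures it. The group main effect compares averages of the pre-test and post-test. Under randomisation the pre-test carries no treatment effect, so only half of the post-intervention difference remains. The time main effect measures change averaged over all arms, whether or not the arms differ.

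The rule as written therefore ties the pairwise comparisons to a term other than the one the trial was sized for. This matters most in the three-group ANOVA. There the contrasts of PET with control, PET + BLE with control, and PET + BLE with PET all wait on this condition, and the last of them answers the second aim stated in the Discussion. The rule covers every outcome, including sleep quality, the main variable for the sample size.

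**Working it through.** **Inputs from section 2.6.** f = 0.4, α = 0.05, power 0.90, 24 per group needed. **Assumed, because the article does not give it:** pre-post correlation r = 0.3, 0.5 or 0.7, with equal variances at the two occasions and equal expected baselines.

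**1. The plan's own figure.** One-way ANOVA on k groups of n, noncentral F with λ = f²·k·n. For k = 4 and n = 24, λ = 0.16 × 96 = 15.36 and power is 0.912, and 24 is the smallest n that reaches 0.90. The stated figure reproduces for four groups. The planned ANOVAs have three and two groups, so at n = 24 the interaction has power 0.853 (λ = 11.52) and 0.774 (λ = 7.68). That shortfall is a separate matter; these two values are the comparators below.

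**2. Effect size carried by each term.** Let the between-group spread of treatment effects on the post value be s, in units of the outcome SD.

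- Interaction (change score): f = s / √(2(1−r)), set to 0.4.
- Group main effect (mean of pre and post): f_main = (s/2) / √((1+r)/2) = 0.4·√((1−r)/(1+r)).
- ANCOVA (post adjusted for pre): f_anc = s / √(1−r²) = 0.4·√(2/(1+r)).

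Example, r = 0.5, three groups: f_main = 0.4 × √(0.5/1.5) = 0.231, so λ = 0.231² × 72 = 3.84, against 11.52 for the interaction. f_anc = 0.4 × √(2/1.5) = 0.462, so λ = 15.36.

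**3. Power at 24 per group.**

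| | r | Group main effect | Interaction | ANCOVA |
|---|---|---|---|---|
| 3 groups | 0.3 | 0.58 | 0.85 | 0.97 |
| | 0.5 | 0.39 | 0.85 | 0.94 |
| | 0.7 | 0.22 | 0.85 | 0.91 |
| 2 groups | 0.3 | 0.51 | 0.77 | 0.92 |
| | 0.5 | 0.35 | 0.77 | 0.88 |
| | 0.7 | 0.21 | 0.77 | 0.84 |

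Simulation (10,000 trials per scenario, both active arms improving equally and control unchanged) agrees for the group and interaction columns. Among three-group trials with a significant interaction, 42%, 62% and 78% (r = 0.3, 0.5, 0.7) had a non-significant group main effect, so no post hoc test would follow.

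**4. If a time main effect also counts.** In the same three-group simulations, at least one main effect was significant in more than 99% of trials, so few true effects are missed. For two groups the figures were 89%, 86% and 82%.

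Now suppose that no group differs and all share a change of d SD (assumed d = 0.3 to 0.5). With N = 72, λ = N·d² / (2(1−r)) on 1 and 69 degrees of freedom. For r = 0.5 and d = 0.3, λ = 72 × 0.09 / 1 = 6.48 and power is 0.71.

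| r | d = 0.3 | d = 0.5 |
|---|---|---|
| 0.3 | 0.56 | 0.94 |
| 0.5 | 0.71 | 0.99 |
| 0.7 | 0.90 | about 1.00 |

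In simulation with d = 0.5 the interaction was significant in about 5% of these trials, as it should be.

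**The case against.** The best defence is that the wording is loose and the intent is clear. Section 2.7 speaks of comparisons within and between groups and of pre/post intervention effects, and section 2.6 targets change. All of this points to the interaction, and a journal article condenses a fuller plan. That may be what the authors meant. But the article does not leave the rule open. It states one, and the term it names is not the one that section 2.6 requires.

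Four stronger readings are tempting, and the document does not support them.

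- **That the rule both hides true effects and fires on shared change.** These harms belong to different readings. Effects are missed if the trigger is the group main effect alone. Shared change fires it only if time counts too, and then few true effects are missed in the three-group ANOVA.
- **That 56% to 100% is a false-positive rate for treatment.** It is how often the condition is met. With a shared 0.5 SD change and no group difference, Tukey contrasts of change between groups were significant in only 4% to 5% of simulated trials. Harm needs Tukey's test on within-group or cell means, and the article does not say which means are compared.
- **That regression to the mean makes a large shared change likely because entry requires PSQI > 5.** Screening questionnaires are completed at visit 1 and the outcome pre-test is visit 2, so part of any regression may precede the pre-test. A shared change is possible, but its size is an assumption here.
- **That a change-score analysis is wrong.** In a randomised trial the interaction test is valid and matches section 2.6. ANCOVA is a gain in precision.

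In the two-group GVS ANOVA a Tukey step adds nothing. The two-group powers matter only if the group main effect is itself taken as the treatment test.

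**Conclusion.** The point holds: the stated condition names a different term from the effect the trial was sized to detect, and the right term appears nowhere in the article. Its size depends on how the phrase is read. With group alone, the only factor named, three-group power falls from 0.85 to between 0.58 and 0.22. With time included, the trigger is sensitive but not specific to treatment, and whether that misleads depends on which means Tukey's test compares.

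The power figures rest on an assumed r of 0.3 to 0.7 and on f = 0.4 applying to the change. The direction does not depend on the exact value: f_main is below the interaction's f at every positive r, by a factor of 0.73, 0.58 or 0.42 at the three values used. The documents do not show that the rule would produce false treatment claims.

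**What to change.** In section 2.7, name group and time as factors. Replace the main-effect condition with the group-by-time interaction, as both the test of treatment and the condition for post hoc comparisons. State that Tukey's test is applied to between-group differences in change. At 24 per group and f = 0.4 this gives power 0.85 (three groups) and 0.77 (two groups).

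Preferably, test the group term in an ANCOVA of the post value adjusted for the same measure before the intervention, and take the Tukey-adjusted contrasts from that model. Its variance is (1+r)/2 of the change-score variance: 0.65, 0.75 and 0.85 at r = 0.3, 0.5 and 0.7.

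The cost is about two sentences. The pre-intervention values are already collected, and neither the design nor the sample size changes.

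### The 24 per group gives 90% power only for a four-group omnibus F test; the planned three-group test and the Tukey comparisons with control have less

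*Protocol article*

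**What the plan says.** Section 2.6 (Sample size calculations) sets the aim as "In order to detect relevant differences between groups in the changes from pre-to post-intervention" and states that "we determined a sample size sufficient to detect medium effect sizes (Cohen’s *f* = 0.4". It continues: "Therefore, α = 0.05, and *p* = 0.90, were selected to favor clinically significant effect sizes"; the 0.90 is evidently the power. The result is "A total of 24 participants per group are necessary to examine the hypothesis that interventions impact sleep quality", and "Each of the four groups will consist of 25 participants, resulting in a total of 100 participants". Neither the test, nor the number of groups in it, nor the pattern of means behind f is named.

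Section 2.7 (Statistical analyses) first mentions comparisons across four groups by repeated measures ANOVA. It then names two ANOVAs tied to hypotheses: one of PET, PET+BLE and control, and one of GVS and control. The hypothesis of the first is that the interventions "will result in improved outcomes in both groups compared to the control group". On pairwise comparisons, post hoc "analyses will be conducted when a significant main effect is observed using Tukey’s test to correct for multiple comparisons".

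**The concern.** An omnibus F test shows only that some group differs. The hypothesis of the first ANOVA is about two particular differences: PET against control and PET+BLE against control. In the plan, only the Tukey step can establish them. If 90% is the power of a different test, with more groups and no pairwise step, a reader will take a non-significant PET result as coming from a comparison with 90% power when its power was lower. The sizing, the hypothesis and the decision step are all printed, and they do not fit together.

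**Working it through.** **Inputs.** From 2.6: f = 0.4, alpha = 0.05, power 0.90, 24 per group needed, 25 enrolled. From 2.7: three groups in the first ANOVA, Tukey after a significant F. Assumptions: f applies to pre-to-post change (as 2.6 implies), changes are normal with a common SD, tests are two-sided, and the gate is the group-by-time F. (The text says main effect, but an intervention effect on change is the interaction.)

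**Step 1: reproduce the 24.** Power of the F test with k groups of n: noncentral F with k − 1 and k(n − 1) df and λ = k·n·f².

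| Groups | λ at n = 24 | Power, n = 24 | Power, n = 25 | n per group for 90% |
|---|---|---|---|---|
| 4 | 96 × 0.16 = 15.36 | 91.2% | 92.4% | 24 (n = 23 gives 89.8%) |
| 3 | 72 × 0.16 = 11.52 | 85.3% | 86.9% | 28 |
| 2 | 48 × 0.16 = 7.68 | 77.4% | 79.2% | 34 |

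Only four groups give 24.

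**Step 2: turn f into a difference from control.** f is the SD of the group means divided by the within-group SD; d is the exercise effect over control in SD units.
- Three groups (0, d, d): f = d√2/3, so d = 0.849.
- Four groups (0, d, d, d): f = d√3/4, so d = 0.924.
- Four groups (0, d, d, c·d), with GVS at a fraction c of the exercise effect: f = d·√[(2 + c²)/4 − ((2 + c)/4)²]. This gives d = 0.800 (c = 0), 0.965 (c = 1/2) and 0.980 (c = 2/3). The spread per unit d is smallest at c = 2/3, so d is largest there.
- Three groups, PET at half of PET+BLE (0, d/2, d): f = d/√6, so d = 0.980 and PET = 0.490.

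**Step 3: power of the comparisons with control.** At least 300,000 simulated trials per pattern, three-group ANOVA, n = 24, 69 error df. Required: F significant at 5%, then Tukey critical t = q(0.95; 3, 69)/√2 = 2.395.

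| Pattern | d | Per arm | Both arms |
|---|---|---|---|
| f over three groups, equal exercise effects | 0.849 | 70% | 57% |
| f over four groups, GVS no effect | 0.800 | 64% | 50% (49.6%) |
| f over four groups, all active arms equal | 0.924 | 78% | 67% |
| f over four groups, GVS at 1/2 | 0.965 | 82% | 72% |
| f over four groups, GVS at 2/3 | 0.980 | 84% | 74% |
| f over three groups, PET at half of PET+BLE | 0.490 / 0.980 | 25% / 83% | 24% |

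With 25 analysed per group, the first and third rows rise to 59% and 70% for both arms.

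**Step 4: where the loss arises.** Without the F gate, power for both arms is the same to three decimals (0.567 in the first row), and per-arm power changes by at most 0.4 points. With unadjusted tests behind the gate (critical t 1.995), the first row would be 72% for both. The loss therefore comes from sizing on four groups, from Tukey's critical value and, for the joint claim, from needing both results.

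**Step 5: effect of baseline adjustment.** With equal pre and post variances and correlation ρ, the ANCOVA residual SD is √((1 + ρ)/2) times the SD of change. For the first row, with Tukey kept (68 error df):
- ρ = 0.3: 0.849/0.806 = 1.053; both arms 82%.
- ρ = 0.5: 0.849/0.866 = 0.980; both arms 74%.
- ρ = 0.7: 0.849/0.922 = 0.921; both arms 67%.

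**The case against.** **No joint success rule is defined.** Section 2.7 states an expectation about both groups, and the Discussion lists the effect of remote training and the added value of light as separate aims. This stands, so the both-arm figures apply only if both results are wanted. Per-arm power is still only 64–84% with equal exercise effects.

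**Section 2.6 ties its 90% to whether interventions affect sleep quality, which an omnibus test addresses.** That is fair, but the four-group test that delivers it is neither of the two hypothesis-specific ANOVAs. If the general four-group sentence in 2.7 is taken to govern, Tukey over four groups with all active arms equal gives 72% per arm and 58% for both, so that reading does not restore 90%.

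**A reader might infer that 57–67% is a ceiling.** It is not: an intermediate GVS effect gives up to about 74% at n = 24.

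**A reader might also infer that an F gate followed by Tukey corrects twice, so that Tukey should give way to unadjusted comparisons (protected LSD).** The documents do not support that as a required change. Tukey is valid, and the gate costs almost nothing. Protected LSD controls the family-wise error only when exactly three groups enter the test. If four enter, three being equal and one different, its simulated error is 12.2%. It also gives up simultaneous intervals.

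**The article condenses a fuller protocol.** This would excuse an omission. Here the printed sample size and the printed analyses disagree.

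**Conclusion.** The point holds as a mismatch between the power claim and the planned tests; the validity of the tests is not in question. The 90% belongs to a four-group omnibus F test. The planned three-group F test has about 85% at n = 24. With equal exercise effects, the comparisons with control have about 70% per arm and 57% for both if f = 0.4 refers to the three analysed groups. If it refers to four groups, they have about 64–84% per arm and 50–74% for both, with the GVS effect ranging from none to equal to that of exercise. Power is lower if PET is less effective than PET+BLE; the half-effect case (24% for both) is an illustration, since the article gives no expected ratio. All figures assume normal changes with a common SD and read the gate as the group-by-time F.

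**What to change.** 1. In 2.6, state that the 90% applies to a four-group omnibus F test only. Print the power of the planned three-group F test (about 85% at n = 24) and of the Tukey comparisons with control, per arm and for both, with the pattern of means assumed.
2. In 2.7, test the group differences in a model of the post value with the baseline value as covariate (ANCOVA), and keep Tukey. In the three-group equal-effect case this raises power for both arms from 57% to about 74% at an assumed correlation of 0.5 (82% at 0.3, 67% at 0.7).

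Replacing Tukey by protected LSD is an optional preference, valid only if exactly three groups enter the test.

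Cost: wording in two sections and a less favourable printed power. No extra participants are needed, and the baseline values are already collected. The changes narrow the gap but do not bring the joint claim to 90%; for scale, both Tukey comparisons on change scores would need about 44 per group at d = 0.85 or 37 at d = 0.92.

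### Section 2.7 ties the Tukey comparisons to a main effect and never names the group-by-time interaction, the effect on which section 2.6 sizes the trial

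*Protocol article*

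**What the plan says.** Section 2.6 gives the target of the sample size: "In order to detect relevant differences between groups in the changes from pre-to post-intervention". The effect size is Cohen's f = 0.4, alpha is 0.05, and the printed value of 0.90 is evidently power. The result is 24 evaluable participants per group.

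Section 2.7 describes the analysis: "Comparisons within and between four groups at baseline and post-intervention will be done using repeated measures ANOVA". It then assigns the roles of the variables: "Assessments will be considered as the dependent variables, and the group will serve as the independent variable". Tukey-corrected post hoc "analyses will be conducted when a significant main effect is observed".

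Two ANOVAs follow. The first compares physical exercise training (PET), PET plus bright light exposure, and control. The second compares GVS with control. Each is said to look for pre/post intervention effects, and each hypothesis is improvement relative to control. Section 2.7 names neither time as a factor, nor the group-by-time interaction, nor a change score.

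**The concern.** With two time points, a between-group difference in change is exactly the group-by-time interaction. Section 2.6 therefore sizes the trial on one term, while the only trigger stated in section 2.7 belongs to another.

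Neither main effect answers the stated hypothesis:

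- **Group.** This effect averages the post-test with the pre-test. Randomised groups are equal at pre-test in expectation, so the average carries half the treatment contrast.
- **Time.** This effect responds to any change common to all arms, such as practice on cognitive tests or habituation to home polysomnography. It says nothing about a difference from control.

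The trigger matters most in the three-group ANOVA. An omnibus test cannot say which arm differs, so the questions of whether each exercise arm beats control, and whether light adds to exercise, are reached through the Tukey comparisons. The text also leaves open which main effect is meant and what the Tukey comparisons are made on, and that choice could be settled after the data are seen.

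**Working it through.** **Inputs from section 2.6:** f = 0.4, alpha = 0.05, power 0.90, 24 evaluable per group. **From section 2.7:** k = 3 groups in the first ANOVA and k = 2 in the second. **Assumed, because the article does not give it:** pre-post correlation ρ, taken as 0, 0.3, 0.5 and 0.7, with equal pre and post SD σ.

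**1. The plan's own figure.** A one-way ANOVA on change has noncentrality λ = N·f² with k − 1 and N − k degrees of freedom. With k = 4, f = 0.4, alpha 0.05 and power 0.90, the solution is n = 23.15, rounded up to 24 per group. At 24, λ = 96 × 0.16 = 15.36 and power is 0.912. The stated 24 reproduces as a test on change, that is, on the interaction.

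**2. What a group main effect would see.** Let δ be the treatment effect at post-test.

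- Change score: contrast δ, SD σ√(2(1 − ρ)).
- Mean of pre and post: contrast δ/2, SD σ√((1 + ρ)/2).
- Ratio: f_main = f_change × √((1 − ρ)/(1 + ρ)).

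For f_change = 0.4 this gives f_main = 0.400, 0.294, 0.231 and 0.168 at ρ = 0, 0.3, 0.5 and 0.7.

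**3. Power at 24 per group (noncentral F).**

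| ANOVA | Interaction | Group, ρ = 0 | ρ = 0.3 | ρ = 0.5 | ρ = 0.7 |
|---|---|---|---|---|---|
| Three groups | 0.853 | 0.853 | 0.579 | 0.386 | 0.220 |
| Two groups (GVS) | 0.774 | 0.774 | 0.512 | 0.347 | 0.207 |

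Power is halved at ρ = 0.46 (three groups) and 0.45 (two groups). If f = 0.4 is scaled to the post-test SD instead, three-group power for interaction versus group is 0.710 vs 0.437, 0.853 vs 0.386 and 0.977 vs 0.345 at ρ = 0.3, 0.5 and 0.7. Halving again falls between ρ = 0.4 and 0.5.

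**4. If either main effect opens the Tukey step.** This was simulated with 20,000 replicates, f = 0.4 on change, 24 per group, controls not changing, and ρ = 0.3, 0.5, 0.7.

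- Three groups, both active arms improving (equally, or one by half as much): group or time significant in about 99% or more.
- Three groups, only one active arm improving: about 85%, 79% and 73%.
- Two groups: about 89%, 85% and 82%.

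**5. The same trigger with no intervention effect.** Suppose every arm, control included, shifts by d SD of the change score. The time effect is then a t test with noncentrality d√N and N − k degrees of freedom. The article gives no d, so a range is shown.

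| Assumed shared shift d | Time effect significant, N = 72 | N = 48 |
|---|---|---|
| 0.2 | 39% | 27% |
| 0.3 | 71% | 53% |
| 0.4 | 92% | 77% |

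**The case against.** The strongest reply is that the interaction is what the authors intend. Section 2.6 speaks of differences in change. Section 2.7 speaks of comparisons within and between groups, of pre/post intervention effects, and of hypotheses relative to control. A two-factor repeated measures ANOVA reports the interaction in any case. The sentence on main effects governs only the Tukey follow-up and does not define the omnibus test. This is also a condensed article, and a list of model terms is commonly left to the analysis plan.

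Much of this stands, and it rules out two stronger readings:

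- A reader might infer that the rule costs more than half the power. The documents give no pre-post correlation. The loss is zero at ρ = 0, about one third at 0.3, and exceeds one half only above about 0.45. It also arises only if the group effect is the one meant.
- A reader might infer that a real effect would get no post hoc test and be reported as negative. The article does not say that a significant interaction would be ignored. The text says a main effect without specifying group. If time counts, the step nearly always opens in the case hypothesised, with both exercise arms improving.

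The reply does not remove the point. The article does not leave the trigger open: it states one, and the term is wrong for the hypothesis. Counting the time effect rescues sensitivity only by making the trigger non-specific, as step 5 of the working shows. In the two-group GVS ANOVA, Tukey between groups adds nothing, so the trigger has little role there. What remains is that the test term is not named.

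**Conclusion.** The point holds as a mismatch between the sizing target and the stated decision rule. Section 2.6 rests on the group-by-time interaction, while section 2.7 makes the Tukey comparisons depend on a main effect and names only group.

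- **If the group effect is meant,** power in the three-group ANOVA falls from 0.85 to between 0.58 and 0.22 for ρ from 0.3 to 0.7. If the group term were also taken as the test for GVS, power would fall from 0.77 to between 0.51 and 0.21.
- **If the time effect also counts,** sensitivity is mostly kept (about 99% when both active arms improve and controls do not, about 73% to 85% when only one does). However, the Tukey step can then be opened by a change that all arms share.

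These figures assume f = 0.4 on change, 24 evaluable per group, equal variances and the correlations shown. The chance that a shared trend opens the step depends on its assumed size. That the rule names the wrong term depends on none of these.

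**What to change.** In section 2.7, or in the analysis plan with a note that it supersedes the published sentence, state that:

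1. time (pre, post) is the within-subject factor and group the between-subject factor;
2. the intervention test in each ANOVA is the group-by-time interaction, equivalently the between-group difference in change;
3. Tukey comparisons in the three-group ANOVA are made between groups on change and depend on that interaction;
4. main effects of group or time, and within-group pre/post tests, are descriptive and not evidence of an intervention effect.

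This costs a few sentences. It needs no new data and no additional participants, and it should be settled before outcome data are analysed.

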### Assessments

2.3

Inclusion and randomization will occur at the baseline assessment (visit 1) and will involve the completion of pre-inclusion questionnaires. A pre-intervention visit will take place before the start of the intervention (visit 2) and a 12-week follow-up assessment will occur at the end of the 12-week intervention (visit 3) (Figure 1A). A final assessment will be performed after completion of the 14-week intervention, but only for control and GVS groups (visit 4) (Figure 1B). According to the literature, a typical GVS protocol is short and does not exceed 2 weeks (52). Therefore, the GVS protocol will be shorter than PET and BLE interventions to ensure participant feasibility and acceptability. The two weeks of vestibular stimulation will be scheduled after the 12-week follow-up to ensure consistent design (Figure 1B). The control group will be compared to the PET and PET + BLE group, but also to the GVS group.

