#### PET combined with bright light exposure (BLE)

2.4.2

Participants in the BLE group will receive the same remote exercise training intervention as the PET group. The PET intervention will be supplemented with 12 weeks of bright light exposure sessions at home. Each participant will be provided with a light lamp (DAYVIA^®^ 072, France) and will be instructed to self-administer light sessions 5 days a week (from Monday to Friday) for 1 h in the morning (between 8:00 am and 10:00 am). During the sessions, participants will face the 10,000-lux light box at a distance of 50 cm and 45° from the eyes, avoiding direct staring to minimize discomfort. The intervention will be remotely monitored on the SAPATIC digital platform, in specific: exposure days, exposure time, and remarks filled in by the participants.

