## Discussion

3

This study aims to demonstrate the positive impacts of non-pharmaceutical remote interventions (PET, the complementary contribution of BLE to PET, and the specific contribution of GVS) on sleep quality. The study also aims to demonstrate how these interventions can result in improvements in circadian rhythms, overall sleep, physical and motor fitness, cognition, QoL, and mood parameters.

Although the benefits of physical activity on individuals’ health are widely acknowledged (21, 22, 29–31), few studies have examined the efficacy of PET using videoconferencing on fitness, cognition, QoL, and mood parameters in healthy older adults (37–39) and none on sleep. Moreover, current literature supports the advantages of remote physical training conducted through videoconferencing (39, 41, 75, 76). Our primary aim is to determine whether this training modality also yields positive effects on sleep. The second aim is to determine whether the addition of remotely monitored self-administered BLE to videoconference physical exercise training can optimize sleep improvements. Studies exploring the impact of combining these two synchronizers are still rare, focusing primarily on quality of life and mood (77, 78), with none specifically addressing sleep.

Studies conducted in both animals and humans have suggested a connection between the vestibular system and circadian rhythm (42, 43). There has been limited rigorous research on the effect of GVS on sleep quality, particularly in cases of insomnia sleep disorders. Krystal et al. (46) showed, using polysomnography, that galvanic vestibular stimulation induces a reduction in sleep latency only in participants whose sleep latency was greater than or equal to 14 min. Goothy and McKeown (79) observed a significant decrease in the ISI scores in healthy adults, indicating improvements in subjective sleep parameters following the GVS protocol. These studies provide preliminary evidence of the specific contribution of GVS on sleep quality, but none have been conducted in healthy older adults with sleep complaints. Further research is needed to assess the role of vestibular stimulation as a non-photic stimulus in synchronizing circadian rhythms.

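### The Discussion asks what bright light adds to exercise, but the only hypothesis for the three-arm ANOVA is against control and can be met when light adds nothing

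*Protocol article*

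**What the plan says.** The Discussion (section 3) describes the light question as one of increment: "The second aim is to determine whether the addition of remotely monitored self-administered BLE to videoconference physical exercise training can optimize sleep improvements". It also lists "the complementary contribution of BLE to PET, and the specific contribution of GVS" among the effects to be demonstrated.

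Section 2.4.2 fixes what separates the two arms: "Participants in the BLE group will receive the same remote exercise training intervention as the PET group". Light is the only planned difference between them.

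Section 2.7 analyses PET, PET + BLE and control in a first repeated-measures ANOVA. The hypothesis attached to it is that "the combined PET and light interventions will result in improved outcomes in both groups compared to the control group". The general objective in that section is also framed against control, as is section 2.3: "The control group will be compared to the PET and PET + BLE group, but also to the GVS group". Tukey's test is to follow if a main effect is significant. No sentence states a hypothesis that PET + BLE differs from PET.

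**The concern.** An aim about what light adds needs a comparison that isolates light. Since both arms get the same exercise, that comparison is PET + BLE minus PET. The written hypothesis has two parts, PET better than control and PET + BLE better than control, and both hold if exercise works and light is inert. Meeting it therefore gives no information on the increment.

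At stake is what the trial may conclude about light. The relevant contrast is tied to no aim, is reached only through the omnibus test, and has to be picked out afterwards from three Tukey pairs. A reader left with the two control comparisons could credit light because one was significant and the other was not, or dismiss it because both were.

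**Working it through.** **1. The plan's own figure.** Section 2.6 gives f = 0.4, α = 0.05 and 0.90 (printed as p, read here as power), with 24 per group. For a one-way ANOVA with k groups the noncentrality is λ = f² × k × n. With k = 4 and n = 24, λ = 0.16 × 4 × 24 = 15.36 and power is 0.912; n = 23 gives 0.898. The 24 reproduces. It is a four-group omnibus figure and says nothing about any single pair.

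**2. Aim and hypothesis side by side.**

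| Place | Question posed | Contrast that answers it |
|---|---|---|
| Discussion | Does adding light to exercise improve sleep further? | PET + BLE minus PET |
| Section 2.7, first ANOVA | Do both exercise arms improve compared with control? | PET minus control; PET + BLE minus control |

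**3. How often the stated hypothesis is met when light adds nothing.** Setup: 40,000 simulated trials per value of d, three arms of 25, change scores with SD 1, PET and PET + BLE both shifted by d from control, three-group F test at 5% followed by Tukey. The documents give no pairwise effect, so d is an assumption and a range is shown. As a reference point, f = 0.4 spread over three arms as (0, d, d) means d × √2 / 3 = 0.4, so d = 0.85.

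| Assumed d | Both arms beat control | Only PET + BLE beats control: Tukey alone | Same, after a significant F test | Tukey pair wrongly favours light |
|---|---|---|---|---|
| 0.4 | 7% | 10% | 9% | 1% |
| 0.6 | 24% | 16% | 15% | 1% |
| 0.8 | 52% | 15% | 14% | 1% |
| 1.0 | 79% | 8% | 8% | 1% |
| 1.2 | 94% | 3% | 3% | 1% |

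At d = 0.85 both arms beat control in about 59% of trials.

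**4. Precision of the contrast that answers the aim, 25 per arm.**
- Single contrast: t(0.975; 48) × √(2/25) = 2.011 × 0.283 = 0.569 SD.
- Tukey pair among three arms: q(0.95; 3, 72)/√2 × √(2/25) = 2.393 × 0.283 = 0.677 SD.

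**5. Power of that contrast, 25 per arm, for an assumed light increment.**

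| Increment d | Single two-sided 5% test | Tukey pair | n per arm for 90% (single contrast, normal approximation) |
|---|---|---|---|
| 0.3 | 0.18 | 0.10 | 234 |
| 0.5 | 0.41 | 0.27 | 85 |
| 0.8 | 0.79 | 0.67 | 33 |

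**The case against.** The strongest reply is that the comparison is already planned. Tukey over three arms tests every pair, so PET + BLE versus PET comes out adjusted for multiplicity beside the two control comparisons. That stands: it would be wrong to say that the plan has no route to the light effect.

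A reader might also infer that the plan will judge light by setting two significance verdicts against control side by side, and that the 15–16% frequency of the misleading pattern at d = 0.6 to 0.8 is therefore a false-positive rate. The documents do not support this. No section says light will be judged that way, the direct Tukey pair wrongly favours light in only about 1% of trials, and 15–16% is the peak of a range running from about 3% to 16%. It measures how often results could be misread.

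Third, the Introduction and Abstract speak of the combined effects of exercise and light, which can reasonably be tested against control. This also stands, but the Discussion's wording on addition and complementary contribution cannot be read that way, and the Discussion calls it an aim.

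Last, linking contrasts to aims is often left to an analysis plan. Here, however, the article does state one hypothesis per ANOVA, and the one covering the light arm does not match the stated aim. That is a mismatch between two things the article fixes, not a detail left out.

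**Conclusion.** The point holds as a mismatch between a stated aim and the stated hypothesis. The hypothesis can be satisfied with no effect of light, in about 7% to 94% of trials as the assumed exercise effect runs from d = 0.4 to 1.2. The contrast that answers the aim exists only as an unnamed, conditional Tukey pair. Pre-specifying it would raise power from about 0.27 to 0.41 for an increment of 0.5 SD and narrow the interval from ±0.68 to ±0.57 SD. Even then the increment is estimated imprecisely.

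The logical mismatch rests on the text alone. The frequencies and powers rest on assumed d values, normal change scores with equal variance, and 25 analysed per arm. Section 2.7 excludes drop-outs and participants who deviate from the protocol, so the analysed number may be smaller and the precision lower.

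**What to change.** In section 2.7:
- State the hypothesis that change in the main sleep variable from visit 2 to visit 3 differs between PET + BLE and PET.
- Test it as one pre-specified contrast for the aim that the Discussion calls the second, and report the estimate with its 95% CI whatever the omnibus result.
- State that any conclusion on light rests on this contrast and not on the two comparisons with control.
- State that, with a half-width near 0.57 SD, a non-significant result does not show that light adds nothing.

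The cost is one additional 5% test outside the Tukey family, a small addition to multiplicity that should be declared. If the team prefers to keep the contrast inside Tukey, it should still be named and reported regardless of the omnibus result, and the half-width is then about 0.68 SD. The other cost is an open admission that the light increment is estimated imprecisely. No new data, participants or visits are needed.
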